## Abstract

**Background:**

Family history is a known risk factor for type 2 diabetes (T2DM), and more so in the presence of overweight. This study aims to develop and evaluate the effectiveness of a new lifestyle education programme 'DiAlert' targeted at 1st degree relatives of people with T2DM and overweight. In view of the high risk for diabetes and cardiovascular disease in immigrants from Turkish origin living in Western Europe, a culturally appropriate Turkish version of DiAlert will be developed and tested.

**Methods/design:**

In this RCT, 268 (134 Dutch and 134 Turkish) overweight 1st degree relatives of patients with T2DM will be allocated to either the intervention or control group (leaflet). The intervention DiAlert aims to promote intrinsic motivation to change lifestyle, and sustain achieved behaviour changes during follow-up. Primary outcome is weight loss. Secondary outcomes include biological, behavioural and psychological indices, along with process indicators. Measurements will take place at baseline and after 3 and 9 months. Changes in outcomes are tested between intervention and control group at 3 months; effects over time are tested within and between both ethnic groups at 3 and 9 months.

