**Figure 1 F1:**
[figure not shown]
**Participant flow**. A detailed participant flowchart of the DiAlert study

Information is lacking on the standard deviation of the percentage of weight change over 3 and 9 months of follow-up in a population at risk for T2DM due to family history and overweight. This study is powered to detect a difference of at least 3.5% body weight at 3 months after randomisation (derived from DPP [8]). Assuming a conservative standard deviation of 6%, a power of 80%, and a significance of 0.05 we require a sample size of 50 participants per group at that time point. If during initial screening T2DM is assessed participants will be excluded from the study (10%). Furthermore, we assume an attrition rate of approximately 15%. Therefore we aim to over sample (25%), and include 67 persons in each group (Dutch group: 67/67 Turkish group: 67/67)

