### Outcome measures

The main outcome measure is change in body weight. Secondary outcome measures include biological, behavioural and psychological outcomes and perceived health status. Predictors for weight loss and health behaviour change (e.g. participant characteristics: gender, initial BMI, SES, number of family members with diabetes, perceived risk and perceived seriousness of diabetes) will be assessed.

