### Measurements

Baseline measurements are planned after randomisation and follow-up measurements are planned at 3 and 9 months (see Figure 1 for a detailed flowchart). Baseline and follow-up measurements include physical measures, laboratory tests and questionnaires.

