### Statistical analysis

Descriptive statistics will be applied to describe the study population at baseline. To determine the effect of the intervention on weight loss and to follow individual change over time we will use generalized linear mixed models and take into account different settings (e.g. intervention groups, trainers), clustering of family members and correlation between observations from same subject; i.e. using a three level structure. Potential confounders and effect modifiers (e.g. BMI at baseline, SES, gender and age) will be investigated. To test predictors of weight loss multiple regression analysis techniques will be performed. The level of significance is set at p < 0.05.

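### The article describes between-arm tests of change and fixes no adjustment of secondary outcomes for their own baseline; stating that adjustment would be a modest, nearly free gain in precision

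*Protocol article*

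**What the plan says.** Directly after listing the primary and secondary outcomes, the abstract says that "Changes in outcomes are tested between intervention and control group at 3 months". It adds that effects over time will be tested within and between the ethnic groups at 3 and 9 months.

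The Outcome measures section gives the scope: "Secondary outcome measures include biological, behavioural and psychological outcomes and perceived health status". Under Measurements, "Baseline and follow-up measurements include physical measures, laboratory tests and questionnaires", so these outcomes have a baseline value. The same section fixes the timing: "Baseline measurements are planned after randomisation and follow-up measurements are planned at 3 and 9 months".

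The Statistical analysis section says: "To determine the effect of the intervention on weight loss and to follow individual change over time we will use generalized linear mixed models". The model is to allow for settings, family clustering and "correlation between observations from same subject; i.e. using a three level structure". On covariates it says only that "Potential confounders and effect modifiers (e.g. BMI at baseline, SES, gender and age) will be investigated". It names no model for the secondary outcomes, and does not say whether baseline enters as a response or as a covariate.

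**The concern.** A change score subtracts the baseline with weight 1. With equal SDs at the two visits, the weight that minimises variance is r. When r is below 1, full subtraction adds baseline noise to the comparison, and more so the lower r is. Part of any chance baseline difference between the arms also passes into the estimate.

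The secondary outcomes include questionnaire scales and self-reported diet and activity, for which r may be moderate. The sample size rests on body weight alone, yet under Aims of the trial the authors expect significant changes in metabolic, psychological and behavioural measures. Precision on those measures is therefore worth protecting.

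Naming a mixed model does not settle the matter. If baseline is one of the repeated responses, each arm has its own free mean at each visit and the data are complete, the model returns exactly the difference in mean changes. A baseline covariate, or a baseline mean common to both arms, recovers the precision. The article states neither.

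**Working it through.** **Inputs.** From the sample-size paragraph under Study design: a difference of 3.5% body weight, SD 6%, power 80%, significance 0.05 (taken as two-sided), 50 per group analysed and 67 recruited, in each of two ethnic groups. Assumed, because the article gives no figure: r from 0.3 to 0.9, equal SDs at baseline and follow-up, and an illustrative effect of 0.5 SD. Clustering is ignored here.

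**The plan's own figure.** The article says "This study is powered to detect a difference of at least 3.5% body weight at 3 months after randomisation". The normal approximation gives n = 2(1.96 + 0.842)² × 6² / 3.5² = 46.1, so 47 per group; the t-test solution is 47.1, so 48. The stated 50 is close and slightly generous (power about 82%). Oversampling: 50 / 0.75 = 66.7, so 67. These figures concern percentage weight change, and the present point leaves them untouched.

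**Variance.** In units of the outcome's SD:
- unadjusted change: 2(1 − r)
- baseline-adjusted value: 1 − r²
- ratio, adjusted to change: (1 − r²) / [2(1 − r)] = (1 + r)/2

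| r (assumed) | Change | Adjusted | Reduction | 50 per arm on change is worth |
|---|---|---|---|---|
| 0.3 | 1.40 | 0.91 | 35% | 32.5 |
| 0.5 | 1.00 | 0.75 | 25% | 37.5 |
| 0.7 | 0.60 | 0.51 | 15% | 42.5 |
| 0.9 | 0.20 | 0.19 | 5% | 47.5 |

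A simulation with 50 per arm (4,000 runs) gave variance ratios, change to adjusted, of 1.32 at r = 0.5 and 1.18 at r = 0.7. The formula gives 1.33 and 1.18.

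**Power for 0.5 SD.** Power = Φ(0.5 √(n/2) / s − 1.96), where s is the square root of the variance above.
- One ethnic group, n = 50 per arm, r = 0.5: change Φ(2.50 − 1.96) = 70%; adjusted Φ(2.89 − 1.96) = 82%. At r = 0.3 the figures are 56% and 75%; at r = 0.7, 90% and 94%.
- Both groups pooled, n = 2 × 50 = 100 per arm, r = 0.5: change Φ(3.54 − 1.96) = 94%; adjusted Φ(4.08 − 1.96) = 98%.

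**Chance baseline gaps.** Given an observed gap g between the arms, the change-score estimate shifts on average by −(1 − r)g. At r = 0.5, a gap of 0.3 SD shifts it by 0.15 SD. With 50 per arm the standard error of the gap is √(2/50) = 0.20 SD, so a gap above 0.3 SD in either direction has probability 2[1 − Φ(1.5)] = 13%. With 100 per arm the standard error is 0.141 SD and the probability is 2[1 − Φ(2.12)] = 3.4%.

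**Change or follow-up value as response.** If F = a + θ·arm + βB + e, then F − B = a + θ·arm + (β − 1)B + e. The arm effect θ is the same. The simulation confirmed this to rounding error.

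**The case against.** The strongest objection is that the article never says the tests are unadjusted. One might infer from the abstract that adjustment for baseline has been ruled out. The text does not support that: the sentence is a general summary covering all outcomes, it names no model, and a change adjusted for baseline gives the same arm effect as an adjusted follow-up value. The word changes can therefore stand. A fuller plan may specify the model for each secondary outcome, and an article need not. This objection stands against any claim of error. What remains is that the only between-arm test described is one of changes, with no own-baseline term beside it. The closest term named is baseline BMI, which bears on weight and is only to be investigated.

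One might also infer that unadjusted changes would bias the trial. They would not: over randomisation they are unbiased, and the carry-over is conditional on the gap that happens to occur.

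Two further limits stand. It is tempting to treat all these measures as noisy, but under Physical measures waist is taken twice and the blood pressure paragraph provides for duplicate readings that are averaged, which tends to raise r. And the larger power gains apply within one ethnic group; in a pooled analysis little is gained at 0.5 SD.

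**Conclusion.** The point holds as a modest improvement in precision. The article describes tests of change and fixes no own-baseline adjustment for any secondary outcome. If those tests are unadjusted, the avoidable variance is 35% at r = 0.3, falling to 5% at r = 0.9. The power consequence is appreciable within one ethnic group and small when the groups are pooled.

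The direction holds for any r below 1 under equal SDs. The size rests on r and on the effect size, neither of which the article gives for a secondary outcome. Clustering would lower the powers under both analyses. The primary sample size is unaffected, and no invalid test or biased estimate has been shown.

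**What to change.** State that each continuous secondary outcome at 3 and 9 months, expressed as follow-up value or as change, is compared between arms with its own baseline value as a covariate, keeping the clustering terms used for weight. If the intended comparison is within each ethnic group, say so and report the effects by group. Mean changes can still be shown descriptively. If this is already intended, stating it closes the point.

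The cost is one or two sentences, with no new data and no change in sample size. The downside is that participants without a baseline value for an outcome need imputation.

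A longitudinal model with one baseline mean common to both arms would avoid that, but it assumes that baseline is unaffected by allocation. The Measurements section places baseline after randomisation, and the Discussion says that participants cannot be blinded. That model should be used only if baseline is obtained before participants know their allocation, which the article does not say. Self-reported baselines influenced by known allocation would also affect change scores and covariate adjustment, so this is no reason to prefer unadjusted change.

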**Discussion:**

The DiAlert intervention is expected to be more effective than the control condition in achieving significant weight loss at 3 months, in both Dutch and Turkish Dutch participants.

**Trial registration:**

Netherlands National Trial Register (NTR): NTR2036

## Background

The prevalence of people with type 2 diabetes (T2DM) in the general population is reaching epidemic proportions in many countries, with the total number of people with T2DM projected to rise to 366 million in 2030 worldwide [1]. It is therefore imperative that strategies to prevent the disease are implemented, this might include targeting high-risk populations to increase effectiveness. The increased prevalence is associated with lifestyle dependent risk factors, including being overweight, physical inactivity and unhealthy diet. In addition, the chance of developing T2DM is two to fourfold greater for people with a positive family history (FH) compared to those without, depending on the number of and the distance to the affected family members [2-4]. Since members of families share the same variations of genes, environment and behaviour patterns, family history information could possibly be used for screening and as a vehicle to motivate people at risk for T2DM to change behaviour [5,6]. However, targeting people with a positive family history of T2DM to promote lifestyle changes is an under-explored prevention strategy. In a review [7] we found only three randomised studies in the literature that have reported on the effectiveness of lifestyle-oriented interventions specifically targeted at individuals with a FH of diabetes. Remarkably, none of these trials addressed FH risk information and its implications for education strategies to change lifestyle. Risk information based on family history is of substantial importance in the DiAlert education programme.

Evidence from large prevention studies shows that the risk of developing T2DM can effectively be reduced by almost 60% in people at risk for diabetes as a result of lifestyle changes resulting in sustained modest weight loss[8,9], with persistent benefits over a longer follow-up of at least 10 years [10]. Among the participants in the Diabetes Prevention Program in the US 66% of the male and 71% of the female participants had a first degree relative with diabetes [11] and results from the Finnish Diabetes Prevention Study (DPS) have confirmed the effectiveness of weight loss by lifestyle changes to reduce the risk of diabetes independent of genetic or familial risk of T2DM [12].

To date, the majority of the diabetes prevention studies have evaluated intensive lifestyle and behaviour change interventions, most often including frequent sessions and one-to-one counselling. Translating the evidence to public health is a challenge, and there is a clear need for targeted interventions that balance feasibility and effectiveness to fit primary care and community settings [13]. Evidence from a pragmatic education programme (PREPARE) in the UK showed that 3 hours structured group-based education incorporating a pedometer is an effective strategy for improving glucose tolerance in people at risk, even after 24 months[14,15]. This confirms the effectiveness of short theory based educational interventions aimed at people who are at risk for T2DM, yet not medically ill and unlikely to experience serious symptom distress or functional impairments to prevent T2DM.

Increasing evidence suggests that family history information could contribute to tailored health information, which is potentially more effective in promoting lifestyle changes than health information aimed at 'anyone at risk'[6]. We therefore developed DiAlert, a theory-based lifestyle education program aimed at overweight first-degree relatives of patients with T2DM, to help them reduce their risk of diabetes and related cardiovascular disease. The group-based intervention consists of two sessions of 150 minutes of education with focus on achieving moderate weight loss, by means of improved diet and physical activity.

Here we report on the study design of the DiAlert study and the development and evaluation protocol of the randomised controlled trial (RCT). In this RCT the effectiveness of DiAlert will not only be evaluated in an ethnic Dutch population but in a population from Turkish origin living in the Netherlands as well. Turkish people are an important group of immigrants in our country, according to figures from 2010 383,957 people (2.3%) of the Dutch population is of Turkish origin [16] and they have a higher prevalence of T2DM (5.6%) as compared to the Dutch population (3.1%)[17]. The increased risk of T2DM in this group is believed to be due to familial susceptibility interacting with an unhealthy lifestyle, characterized by high energy and saturated fat intake, along with low levels of physical activity, being overweight and low socio-economic status [18-20]. Few studies have looked at targeted lifestyle interventions in this group and most relate to secondary prevention [21,22]. Comparisons between the two ethnic groups could contribute to the external validity of DiAlert in the future.

### Aims of the trial

The primary aim of this randomised controlled trial is to test the hypothesis that DiAlert can be effectively utilised to promote weight loss in individuals with a first degree relative with T2DM and being overweight at three months, and thereby help reduce their risk of developing diabetes. In addition, we expect to observe significant changes in metabolic, psychological and behavioural parameters 3 and 9 months following the intervention.

## Methods/Design

### Study design

The DiAlert-study is a randomised controlled trial (RCT) testing the effectiveness of a lifestyle education programme in two groups: ethnic Dutch participants and participants of Turkish origin living in the Netherlands. We aim to include 134 Dutch and 134 Turkish overweight first degree relatives of T2DM patients. Measurements are scheduled at baseline, 3 and 9 months after the last group session (see Figure 1).

**Figure 1 F1:**
[figure not shown]
**Participant flow**. A detailed participant flowchart of the DiAlert study

Information is lacking on the standard deviation of the percentage of weight change over 3 and 9 months of follow-up in a population at risk for T2DM due to family history and overweight. This study is powered to detect a difference of at least 3.5% body weight at 3 months after randomisation (derived from DPP [8]). Assuming a conservative standard deviation of 6%, a power of 80%, and a significance of 0.05 we require a sample size of 50 participants per group at that time point. If during initial screening T2DM is assessed participants will be excluded from the study (10%). Furthermore, we assume an attrition rate of approximately 15%. Therefore we aim to over sample (25%), and include 67 persons in each group (Dutch group: 67/67 Turkish group: 67/67)

### Study population

Eligible are first-degree relatives of T2DM patients (father, mother, brothers or sisters, sons or daughters), between 25 and 65 years of age, and overweight (Body Mass Index of ≥ 25 or waist circumference > 88 cm for females and > 102 cm for males) from ethnic Dutch or Turkish origin.

Exclusion criteria are: people diagnosed with type 1 or 2 diabetes, currently under medical treatment for ischemic heart disease or cancer, diagnosed with a psychiatric disorder, pregnancy or physically/mentally too impaired to participate in the study (e.g. unable to come to the location of the assessments and interventions) and not being able to write and read in Dutch or Turkish.

### Setting

The study population will be recruited in the area of Amsterdam city, the Netherlands, through two strategies: First, GP practices and outpatient clinics will be approached. Patients from GP practices registered with a positive family history and known overweight will be invited by their GP. The second strategy involves an open recruitment strategy through advertisements in local newspapers, leaflets and posters in pharmacies, waiting rooms of GP practices and outpatient clinics. A website with information for participants and professionals to inform people about the study is made available on the internet (http://www.dialert.nl). People can enrol in the study by sending an e-mail or completing a form to be sent by mail. Participation in the DiAlert study is free of charge for all participants. DiAlert group sessions will be delivered in local GP practices and in the outpatient clinic of the VU University Medical Center in Amsterdam facilitated by certified health educators of PRISMA (Pro-active Interdisciplinary Self-Management) [23], who received an additional 4 hours of specific DiAlert training.

### Treatment allocation

After receiving a signed informed consent form from the participants, randomisation will be performed with sealed envelopes. Members of the same family or household participating in the study will be clustered. This will be done to stimulate cohesion in the intervention groups, and to prevent contamination of the intervention effect due to reciprocal communication about the intervention or control condition among family members.

#### Control group

Participants in the control group receive written information about diabetes risk and lifestyle advice to prevent T2DM and a brochure about heredity and diabetes from the Dutch Diabetes Foundation.

#### Intervention group

Participants allocated to the intervention group will be invited to take part in the group-based intervention. Group size is approximately ten participants and the programme consists of two sessions of 150 minutes over two consecutive weeks and 4 newsletters during the next 6 months. For the timing of newsletter mailings see Figure 1 participants flow.

### Intervention

The DiAlert intervention is based on the theory-based diabetes self-management programme PRISMA that was adapted from DESMOND (Diabetes Education for Self-Management in Ongoing and Newly Diagnosed) for the Netherlands [23,24]. DESMOND and PRISMA (hereafter: PRISMA) consist of two interactive group sessions and have shown to be successful at initiating behaviour change in individuals with T2DM [24]. To adapt the program for participants at risk for T2DM we performed a review of existing lifestyle interventions for people with a positive family history of T2DM [7] and consulted different experts.

DiAlert is based on social cognitive behavioural theories, in particular the Health Action Process Approach (HAPA) [25]. HAPA identifies three key determinants of initial change: risk perception, self efficacy and outcome expectancies, leading to intentions and action for health behaviour change. Table 1 provides an overview of the DiAlert modules and aims. In brief, the sessions include explorations of knowledge, impact and concern about T2DM, discussing risk factors for T2DM, insulin resistance and loss of beta cell function, recommendations for balancing energy intake and energy expenditure, goals setting and action planning.

**Table 1 T1:** Outline of the DiAlert programme for first degree relatives of people with type 2 diabetes

Modules	Duration (min)	Sample activity	Aim
**Session 1**	150 min.		

- Introduction	10	General introduction trainer and observers are introduced.	State aims and proceedings of the two group sessions.

- Participant topics	30	All participants are asked about family members with T2DM, and will be encouraged to explore their knowledge, concern and possible impact of T2DM. Motives for participating and burning questions of participants are listed.	Introduction of participants, personal models about T2DM are explored.

- View on personal risk factors	30	Participants share current knowledge of risk factors for T2DM and discuss modifiable and non-modifiable risk factors.	Increase risk perception

	30	*break*	

- How to prevent T2DM?	30	Participants learn about insulin resistance, loss of beta cell function and the positive effects of body weight loss and physical activity.	Increase outcome expectancies for weight loss and physical activity

- Energy balance	10	Advice based on recommendations on nutrition and physical activity. Balancing calorie intake and energy expenditure per day.	Increase outcome expectancies for weight loss and healthy diet

- Homework assignment	10	Self-monitoring diet and physical activity (diary).	Monitoring current lifestyle behaviour

**Session 2**	150 min.		

- Reflections	10	Summary of session 1: Participants reflect on issues raised by the program so far.	Discussing topics of the first session

- Taking control: Nutrition and exercise balance	40	Introduction to calories by comparing different food products. Reading nutrition fact labels.	Knowledge and skills for food choices (calorie and fat intake) to reduce risk factors

	30	*break*	

- Personal action plan	45	Sharing experiences about losing weight. Exploring benefits and barriers for lifestyle change. Participants' stories are used to summarise possibilities/facilities to lose weight. Participants formulate personal action plans to change lifestyle.	Action planning, coping planning and self efficacy for formulated goals

- Burning questions	15	Check whether all questions raised by participants throughout the two group sessions have been answered and understood.	All questions of participants are answered

- Conclusions	10	Summary	Conclusions of the two session are summarised

